### Process evaluation

A process evaluation will focus on key implementation outcomes,^25^ including acceptability, feasibility and perceived appropriateness of the RISE intervention. Following completion of the post-assessment questionnaire, a purposive sample of approximately 10 participants from the RISE intervention group will be invited to complete a semi-structured interview exploring their experience of the RISE intervention including barriers and enablers to participation and suggestions for improvement. Sampling will aim to capture variation in recruitment site, level of intervention engagement and participant experience to obtain a diverse range of perspectives on acceptability and implementation. Participants will receive $50 for completing a 60-min interview. In addition, patients, health professionals and funders (compulsory third-party (CTP) insurance representatives) (total approximately n=10) will be purposively sampled and invited to participate in a series of 2–3 focus groups (or individual interviews if required) to explore opportunities to optimise and integrate RISE into healthcare settings and insurance system care pathways. Patient participants will receive $50/hour for participating in focus groups. These sample sizes are pragmatic and appropriate for a feasibility study and are intended to capture a range of experiences and perspectives to inform intervention refinement and implementation planning rather than to achieve thematic saturation. Findings from the process evaluation will be used to contextualise feasibility outcomes, including recruitment, retention and intervention engagement and to inform interpretation of preliminary clinical outcomes.

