#### Post-intervention assessments

All participants will be asked to complete an online assessment questionnaire at 6-week post-randomisation and at a 3-month follow-up. The questionnaire is completed online, and participants will be sent a link via email (or SMS) where they can access it. All participants will be remunerated $30 for each questionnaire completed (based on Health Consumer Queensland guidelines).

A summary of the proposed data collection schedule, in accordance with Standard Protocol Items: Recommendations for Interventional Trials (SPIRIT) guidelines, is outlined in table 1.

**Table 1 T1:** Proposed data collection schedule according to SPIRIT guidelines

	Pre-trial		Trial period			
	Week 0		Week 1	Weeks 2–5	Week 6	3 Months
	Eligibility, informed consent	Baseline questionnaire, random allocation	Intervention onboarding	Intervention period	Follow-up 1	Follow-up 2

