### Feasibility outcomes and key feasibility criteria

Feasibility outcomes were selected to reflect key trial processes, RISE intervention engagement, acceptability and the feasibility of collecting outcome and cost data, in line with recommendations for pilot and feasibility studies.^28^ Pre-specified progression criteria will be used alongside information gathered from the process evaluation to determine whether a future definitive RCT is warranted. Criteria are based on a traffic-light system, where green indicates that the feasibility target has been met and progression to a definitive trial is supported; amber indicates that modifications to the protocol are required prior to progression and red indicates that progression to a definitive trial is not currently recommended.

Trial feasibility outcomes (eg, recruitment and retention) will be summarised across all randomised participants, whereas intervention-specific feasibility outcomes (eg, uptake, acceptability and wearable use) will be calculated for participants allocated to the RISE intervention only. Uptake of optional clinician support sessions will be assessed by examining the proportion of scheduled sessions that are completed. Because these sessions are intended to provide additional support where needed, overall demand for sessions will be interpreted descriptively rather than used as a progression criterion. The feasibility outcomes and corresponding progression criteria are presented in table 2.

**Table 2 T2:** Feasibility outcomes and criteria for proceeding to a definitive randomised controlled trial (RCT)

Feasibility outcome	Measurement	Green	Amber	Red
Recruitment	% of eligible participants who consent to participate	70%	50–69%	<50%
	Average number of participants recruited per month	≥4 /month	2–3/month	<2/month
	% who consent to use the wearable device (RISE intervention group only)	50%	30–49%	<30%
Retention	% who complete the outcome assessment at 6-weeks and 3-month assessment	70%	50–69%	<50%
	% who complete the cost-related data questions at baseline, 6 weeks and 3 months	50%	30–49%	<30%
RISE uptake	% of intervention participants who respond to ≥3 interactive SMS prompts during the intervention period (RISE intervention group only)^*^	70%	30–69%	<30%
	% of scheduled psychologist scheduled sessions that are attended (RISE intervention group only)	70%	50–69%	<50%
	% of scheduled physiotherapist scheduled sessions that are attended (RISE intervention group only)	70%	50–69%	<50%

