### Data analysis

Participant characteristics and baseline measures will be summarised using descriptive statistics. As this is a feasibility trial, analyses will be primarily descriptive and will focus on estimating feasibility parameters. Feasibility outcomes (recruitment, retention, intervention engagement, data completeness and acceptability) will be descriptively summarised. These estimates will be interpreted against the pre-defined progression criteria (see table 2) together with the process evaluation data to determine whether a future definitive trial is warranted. Final progression decisions will be made by the Trial Management Committee based on the overall pattern of feasibility findings across domains, together with qualitative process data and consideration of whether any identified barriers are modifiable. Where findings are mixed, decisions regarding progression will consider the pattern of results across domains, the nature and modifiability of barriers and the potential for refinements prior to a future trial. Participant responses regarding treatment allocation will also be summarised descriptively and compared with actual allocation to assess the success of participant blinding. No formal imputation of missing data is planned. The extent and patterns of missing data will be examined as part of the feasibility evaluation of the data collection procedures.

Preliminary changes in patient-reported outcomes will be explored using estimates of between-group differences with 95% CIs at each follow-up time point. These analyses will be conducted on an intention-to-treat basis. As this feasibility study is not powered to evaluate clinical effectiveness, no formal hypothesis testing will be undertaken and estimates will be interpreted cautiously with consideration of the width of the CIs. These exploratory analyses are intended to identify preliminary signals of potential clinical benefit, assess the suitability and responsiveness of candidate outcomes and inform the selection of the primary clinical outcome for a future definitive trial.

Qualitative interview and focus group data will be analysed using reflexive thematic analysis^44

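### As worded, the interview invitation gives no route to RISE participants who never return the post-assessment questionnaire, although the findings are meant to help interpret retention

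*Protocol article*

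**What the plan says.** The Process evaluation section sets the interview recruitment rule: "Following completion of the post-assessment questionnaire, a purposive sample of approximately 10 participants from the RISE intervention group will be invited" to interview. On selection it says: "Sampling will aim to capture variation in recruitment site, level of intervention engagement and participant experience". The interviews are described as "exploring their experience of the RISE intervention including barriers and enablers to participation and suggestions for improvement".

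The same section gives the purpose: "Findings from the process evaluation will be used to contextualise feasibility outcomes, including recruitment, retention and intervention engagement". The Data analysis section then has the Trial Management Committee base progression on the feasibility findings across domains, "together with qualitative process data and consideration of whether any identified barriers are modifiable".

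Retention is one of the traffic-light criteria in Table 2 (Feasibility outcomes and key feasibility criteria). It is the percentage "who complete the outcome assessment at 6-weeks and 3-month assessment", with green at 70%, amber at 50–69% and red below 50%. The follow-up questionnaires go to everyone: "All participants will be asked to complete an online assessment questionnaire at 6-week post-randomisation and at a 3-month follow-up" (Post-intervention assessments).

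**The concern.** The trigger for an interview invitation is completion of a questionnaire. A RISE participant who never completes it has no such event, and no other route is described. If retention turns amber or red, the people best placed to say why are those whom the wording leaves out. The committee would then judge whether a retention barrier can be modified without having heard from anyone who met it.

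A second source does not fill the gap. Experienced acceptability is collected in the 6-week and 3-month questionnaires (Table 1; Acceptability), and no imputation is planned (Data analysis). Interviews and follow-up acceptability scores would therefore miss the same people. The strengths and limitations list presents the qualitative study as a way to triangulate the quantitative feasibility data. Two sources that share a missing group cannot check each other on dropout.

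**Working it through.** The plan gives no figure of its own to reproduce. The check sets the statements side by side and then puts a scale on the group concerned.

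**1. Who is in the interview frame, read literally?**
- Returned the questionnaire, high engagement: in.
- Returned the questionnaire, low engagement or stopped messages: in. All participants are asked for the questionnaire whatever their engagement, and level of engagement is a stated sampling dimension.
- Never returned the questionnaire: no route described.

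**2. Are non-completers sought in another way?** The three sampling dimensions are site, engagement and experience. Withdrawal and non-return are not listed. The focus groups include patients, but their stated task is to optimise RISE and fit it into health and insurance pathways. They are not described as recruiting people who left the trial.

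**3. Who may still be contacted after STOP?** The Overview of intervention period section describes texting STOP as a way to withdraw from the study. The Ethics and dissemination section describes it as opting out of messages. On the first description, someone who texts STOP may never reach the questionnaire. On the second, that person stays in follow-up and in the interview frame.

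**4. Scale.** Inputs: 25 participants in the RISE arm (RCT sample size) and the retention cuts of 70% and 50% (Table 2). Assumption: the overall retention rate applies equally to the RISE arm.
- Green needs at least 0.70 × 25 = 17.5, so 18 completers. Non-completers: at most 25 − 18 = 7 (18/25 = 72%). With 8 missing, 17/25 = 68%, which is amber.
- Amber needs at least 0.50 × 25 = 12.5, so 13 completers. Non-completers: at most 25 − 13 = 12 (13/25 = 52%). With 13 missing, 12/25 = 48%, which is red.

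**5. Which way do these bounds err?** Table 2 retention covers both follow-ups. If the post-assessment questionnaire is the one at 6 weeks, a participant lost only at 3 months counts as not retained but was already open to invitation. The number out of reach is then below 7 or 12. In the other direction, retention is summarised over all 50 randomised participants. If losses fall unevenly between arms, the RISE count could lie above or below these figures.

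**6. When could the invitation be widened without harm?** Table 1 puts the intervention period in weeks 2–5, and the blinding question at week 6 together with the first follow-up outcomes. A RISE-only invitation at the end of messaging would come before both and could reveal allocation. An invitation after the 6-week assessment window has closed would not.

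**The case against.** The strongest reply is that the opening phrase may only fix timing: interviews take place after that assessment point. No sentence excludes non-completers. This reading is possible and limits how firmly the point can be put. It does not remove the point, because the literal wording makes the participant's own completion the trigger, and a site following it would invite completers only.

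A reader might infer something stronger: that anyone who stopped or disengaged cannot be interviewed, so engagement failures go unexplored and acceptability is pushed upward. The article does not support this. Low engagers who return the questionnaire are eligible and are deliberately sought. The acceptability light in Table 2 is scored from the questionnaire, so the choice of interviewees cannot move it.

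It is also fair to say that the plan speaks of context rather than explanation, credits the whole process evaluation rather than the interviews alone, and has other evidence on disengagement: snooze and stop use, diaries, SMS response patterns and patterns of missing data. These stand. They show that a person stopped and when, but apart from what a diary may record they do not show why. The judgement on modifiable barriers needs the reason.

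Finally, a journal article may leave invitation procedures to the full protocol. Silence alone would be no finding. Here the article states a recruitment rule, and that rule does not match the use stated for the findings.

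**Conclusion.** The point holds for non-completers. Read literally, the interview rule reaches only RISE participants who complete the post-assessment questionnaire, and non-return or withdrawal is not a sampling dimension, while the findings are to inform the reading of retention and the progression decision. The size is at most 7 of 25 at green retention and at most 12 of 25 at amber. Both figures assume that overall retention applies equally to the RISE arm, and both fall if some participants are lost only at 3 months. The conclusion also rests on reading the opening phrase as a condition; if only timing was meant, a clarifying clause resolves most of it. It does not extend to low engagers in general, and it does not show that the acceptability result is biased. The change is worth making before interviews begin, because accounts from people who left are hard to recover later.

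**What to change.** - State that all randomised RISE participants become eligible for interview invitation once their 6-week assessment window has closed, whether or not the questionnaire was returned, unless they declined further contact. Waiting for the window to close protects the blinding question and the 6-week self-reported outcomes.
- Add non-completion or withdrawal to the purposive sampling dimensions, and aim for a few of the roughly 10 interviews from this group.
- Say which questionnaire the post-assessment one is.
- Reconcile the two descriptions of STOP (Overview of intervention period; Ethics and dissemination), so that it is clear who may still be contacted.

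The cost is a change of wording, a few more invitations and a lower response among people who disengaged. The number of interviews and the payments are unchanged.

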### RCT sample size

A formal power calculation was not conducted, as this study is designed as a feasibility trial. A target of 25 participants per arm over 12 months is selected to support estimation of key feasibility parameters and to inform planning for a future definitive trial. This sample size is broadly consistent with recommendations for pilot and feasibility trials, which suggest total sample sizes in the range of 24^26^–70 participants.^27^

### Randomisation

Participants will be randomly assigned to the intervention or control condition in a 1:1 ratio using a computer-generated random allocation list. A statistician who is not involved in data collection will generate the allocation sequence. REDCap will then automatically assign consented participants who have completed the baseline assessment in a 1:1 ratio to either the RISE intervention or active control group using a pre-loaded randomisation table. Allocation will be concealed using a secure, centralised randomisation process within REDCap, ensuring that the research team members enrolling participants cannot predict or influence group assignment.

### Blinding and masking

To minimise potential bias in outcome measurement, outcome measures will be collected through REDCap and monitored by a research officer who is blinded to participant allocation. At follow-up, participants will be explicitly instructed not to discuss any details of the study, including their group assignment, with the research officer to protect the integrity of the blinding process.

Participant masking will be supported by providing both groups with SMS contact, without disclosing group allocation. The usual care group (control condition) will receive two text messages a week on general health information related to whiplash and be prompted to access the publicly available *My Whiplash Navigator*. At any stage, patient care and safety will be prioritised over participant blinding and masking procedures.

### Intervention condition: RISE

The RISE intervention is a tailored text message-based intervention to support the recovery journey for patients with acute WAD from an RTI. It is delivered over a 3–4 week period, where messages will be sent to patients targeting two treatment mechanisms identified in prior research: stress symptom management and improved pain coping skills^14^ in addition to recommended exercise and activity. Message content was further developed in line with themes identified from prior work co-designing the intervention (*manuscript under review*). These themes included: 1) What can I expect in terms of RTI symptoms and the recovery process? 2) What can I do to help myself? and 3) What are these unexpected emotions and trauma responses, and are they normal? The timing, intensity and frequency of the messages will be tailored to patient preferences where possible. RISE includes four core domains, which underpin the content of the messages, as outlined:

**R**ecovery-focused messages that provide reassurance, encouragement and emotional support.**I**nformational support providing education on whiplash injury and pain and what to expect during recovery.**S**upport for behaviour change, including psychological techniques.**E**mpowering and motivational messages to enhance patient confidence in managing their pain and recovery.

#### Personalisation of the RISE intervention

The RISE intervention incorporates a range of personalisation features within both message content and delivery to support relevance and responsiveness to individual participant needs and preferences over the intervention period. During onboarding, participants nominate their preferred time of message delivery and are offered the option to schedule one 30-min session with a psychologist and one 30-min session with a physiotherapist trained in StressModex (integrated stress inoculation training and exercise)^13^ at any point during the programme. Throughout the intervention, participants can access additional messages on demand via keyword text requests (eg, CALM, ACTIVATE). At the end of week 1, participants receive a prompt to review message frequency and may choose to reduce frequency for a 24-hour period. In addition, participants can temporarily reduce message frequency at any time by texting SNOOZE. Message content is further tailored during weeks 1–3 based on baseline survey responses (eg, sleep disturbance, concentration difficulties), and participants receive two-way SMS check-ins during this period to rate pain intensity, stress and perceived support. Participants are also invited to complete a brief weekly check-in survey and diary entry to reflect on their experiences. At the end of week 3, participants are offered the option to extend messaging for an additional 3 days. These features provide a structured approach to tailoring intervention delivery while maintaining consistency across participants.

### Active control condition (general health text messages plus an online resource, My Whiplash Navigator)

Participants in the active control group will receive general onboarding messages without options for any intervention or message personalisation. On the first Monday following completion of the onboarding period, they will then receive two messages per week containing general health information and education about WAD recovery and recommended management, including activity and exercise, as well as access to a publicly available website, My Whiplash Navigator. They will receive these messages for the same 3-week period as the intervention group but will not have the option for additional days or clinician-based support.

Messages in both conditions will be delivered using a commercial SMS provider (CellCast, https://www.cellcast.com/au), using a dedicated telephone number. All SMS scheduling and storage will occur within The University of Queensland’s research infrastructure.

### Feasibility outcomes and key feasibility criteria

Feasibility outcomes were selected to reflect key trial processes, RISE intervention engagement, acceptability and the feasibility of collecting outcome and cost data, in line with recommendations for pilot and feasibility studies.^28^ Pre-specified progression criteria will be used alongside information gathered from the process evaluation to determine whether a future definitive RCT is warranted. Criteria are based on a traffic-light system, where green indicates that the feasibility target has been met and progression to a definitive trial is supported; amber indicates that modifications to the protocol are required prior to progression and red indicates that progression to a definitive trial is not currently recommended.

Trial feasibility outcomes (eg, recruitment and retention) will be summarised across all randomised participants, whereas intervention-specific feasibility outcomes (eg, uptake, acceptability and wearable use) will be calculated for participants allocated to the RISE intervention only. Uptake of optional clinician support sessions will be assessed by examining the proportion of scheduled sessions that are completed. Because these sessions are intended to provide additional support where needed, overall demand for sessions will be interpreted descriptively rather than used as a progression criterion. The feasibility outcomes and corresponding progression criteria are presented in table 2.

**Table 2 T2:** Feasibility outcomes and criteria for proceeding to a definitive randomised controlled trial (RCT)

Feasibility outcome	Measurement	Green	Amber	Red
Recruitment	% of eligible participants who consent to participate	70%	50–69%	<50%
	Average number of participants recruited per month	≥4 /month	2–3/month	<2/month
	% who consent to use the wearable device (RISE intervention group only)	50%	30–49%	<30%
Retention	% who complete the outcome assessment at 6-weeks and 3-month assessment	70%	50–69%	<50%
	% who complete the cost-related data questions at baseline, 6 weeks and 3 months	50%	30–49%	<30%
RISE uptake	% of intervention participants who respond to ≥3 interactive SMS prompts during the intervention period (RISE intervention group only)^*^	70%	30–69%	<30%
	% of scheduled psychologist scheduled sessions that are attended (RISE intervention group only)	70%	50–69%	<50%
	% of scheduled physiotherapist scheduled sessions that are attended (RISE intervention group only)	70%	50–69%	<50%
Acceptability†	% sample with usefulness and ease of use mean scores>4.0/5‡ (RISE intervention group only)	60%	40–59%	<40%

Note: Green light indicates the feasibility outcome is achieved and that we can proceed to a full definitive randomised controlled trial (RCT); amber light indicates that changes to the proposal are required before proceeding to a full trial; red light indicates that the feasibility outcome is not achieved and proceeding to a full trial is not recommended.

* Interactive engagement is defined as responding to two-way SMS prompts (eg, check-in ratings). Participants receive approximately three interactive prompts per week on average. Engagement with prompts is encouraged but not required.

† Additional acceptability metrics will include qualitative experience data as part of the process evaluation, self-report responses to the purpose-built and validated questionnaires and behavioural indicators of engagement.

‡ Adapted Technology Acceptance Measure; the mean score is calculated as the mean of items within each subscale. Participants are classified as meeting the criterion if both usefulness and ease-of-use mean scores are ≥4.0.

RISE, recovery, information, support and empowerment; SMS, short message service.

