#### Acceptability

An adapted version of the Technology Acceptance Model (TAM)^29^ will be used to assess perceived ease of use and perceived usefulness of the RISE intervention. Each construct is measured using six items rated on a 7-point scale from 1 (‘Strongly disagree’) to 7 (‘Strongly agree’). Mean scores will be calculated for each subscale, and participants will be classified as meeting the acceptability criterion if both subscale mean scores are≥4.0. TAM items will be framed in the future tense at baseline to assess anticipated acceptability and in the past tense at follow-up to assess experienced acceptability following intervention use.^30^

Additional indicators of acceptability will include responses to purpose-built items, including participant intention to use (or continue using) the intervention, willingness to recommend the intervention to others with WAD and Session Rating Scale scores for participants who complete the clinician-guided session/s.^31^ Intervention-specific items assessing perceived informational support, emotional support, encouragement for behaviour change and confidence in managing recovery will also be included. These items were developed to align with the core domains of the RISE intervention. In addition, behavioural indicators of acceptability will be examined and summarised. These include participant engagement with optional or self-initiated features, such as use of the on-demand message function, ‘snooze’ or ‘stop’ functions and weekly diaries, as well as the frequency of use of these features. Participant feedback on message frequency and perceived helpfulness will also be assessed. These behavioural indicators provide additional insight into patterns of participant engagement beyond the core intervention components. Finally, we will examine time participants wear the device, including the extent of valid data derived from the wearable device.

Patient experience and clinician and funder perspectives, including those of CTP insurance representatives, will be explored as part of the process evaluation. Individual semi-structured interviews and focus groups will examine the perceived value and implementation potential of the RISE intervention as well as opportunities for optimisation. Sessions will be co-facilitated by research staff experienced in co-design and qualitative methods, audio-recorded and transcribed verbatim.

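### The acceptability progression threshold contradicts itself: Table 2 scores it out of 5, but the instrument is described as 1 to 7, and the meaning of 4.0 depends on which is true

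*Protocol article*

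**What the plan says.** The rule appears in three places in the protocol article.

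- **Table 2, Acceptability row:** the measure is the percentage of the "sample with usefulness and ease of use mean scores>4.0/5", in the RISE group only. Green is 60%, amber 40–59% and red below 40%.
- **Table 2, footnote to that row:** "the mean score is calculated as the mean of items within each subscale", and "Participants are classified as meeting the criterion if both usefulness and ease-of-use mean scores are ≥4.0". No scale maximum is given.
- **Acceptability section:** "Each construct is measured using six items rated on a 7-point scale", anchored at strong disagreement (1) and strong agreement (7). It then says "participants will be classified as meeting the acceptability criterion if both subscale mean scores are≥4.0".

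The section on feasibility outcomes says that intervention-specific outcomes such as acceptability "will be calculated for participants allocated to the RISE intervention only". The sample size section gives the planned denominator: "A target of 25 participants per arm over 12 months is selected".

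Table 1 schedules the acceptability questionnaire at baseline, week 6 and 3 months. The Acceptability section says that the baseline items are in the future tense and the follow-up items in the past tense. The Table 2 row names no time point.

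**The concern.** A mean of items scored 1 to 7 is not a score out of 5, and no conversion is described. The row and the Acceptability section therefore cannot both describe the same score. The row also uses a strict inequality, where the footnote and the text allow equality.

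The value 4.0 means different things on the two scales. Out of 5 it asks for clear agreement. On 1 to 7 it asks only that a participant not be below the middle on either subscale. This is the only acceptability row in Table 2, and green is defined as supporting progression to a definitive trial. If the threshold can be read two ways, the reading could be chosen after the ratings are known, which is what a pre-specified traffic-light rule should prevent.

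**Working it through.** **Inputs from the article.** Cut 4.0; scale maximum 5 (Table 2 row) or 7 (Acceptability section); six items per subscale, score = item mean, both subscales must pass; green at 60%; 25 planned in the RISE arm.

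**Step 1. Can the row's maximum of 5 be reproduced?** No. Six items scored 1 to 7 have a mean between 1 and 7, and no rescaling is given.

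**Step 2. Position of 4.0 on each scale.**
- On 1–5: (4 − 1)/(5 − 1) = 0.75 of the range. The midpoint is (1 + 5)/2 = 3.0.
- On 1–7: (4 − 1)/(7 − 1) = 0.50 of the range. The midpoint is (1 + 7)/2 = 4.0.
- 4.0 on 1–5 carried to 1–7: 1 + 6 × 0.75 = 5.5.
- 4.0 on 1–7 carried to 1–5: 1 + 4 × 0.50 = 3.0.

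**Step 3. What the inequality changes on a 1–7 scale.** A participant who ticks 4 on all 12 items has both means at 4.0. That participant passes under the footnote and the text, and fails under the row. The strict form adds little: one item of six at 5 and the rest at 4 gives (5 × 4 + 5)/6 = 4.17, which passes.

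**Step 4. Number needed for green.** 0.60 × 25 = 15 participants, if all 25 complete the scale.

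**Step 5. Illustration of the size, if the scale is 1–7.** The article gives no distribution of ratings, so the spreads are assumptions. Each person has a normally distributed level on each subscale. Items are that level plus noise, rounded and limited to 1–7. The chance of green is the binomial probability of at least 15 of 25 passing both subscales.
- Spread A: between-person SD 1.0, subscale correlation 0.6, item SD 1.0.
- Spread B: 0.7, 0.8 and 0.8 respectively.

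| Average rating | Spread | Pass at ≥4.0 | Chance of green | Pass at ≥5.5 | Chance of green |
|---|---|---|---|---|---|
| 4.0 | A | 37% | 0.02 | 3% | about 0 |
| 4.0 | B | 40% | 0.04 | 1% | about 0 |
| 4.5 | A | 56% | 0.44 | 9% | about 0 |
| 4.5 | B | 67% | 0.83 | 5% | about 0 |
| 5.0 | A | 75% | 0.97 | 19% | about 0 |
| 5.0 | B | 87% | >0.99 | 18% | about 0 |
| 5.5 | A | 88% | >0.99 | 36% | 0.01 |
| 6.0 | A | 95% | >0.99 | 56% | 0.41 |

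With the strict inequality (>4.0), the chance of green is 0.205 (A) to 0.523 (B) at an average of 4.5, and 0.879 to 0.997 at 5.0.

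**The case against.** **The article does not settle which statement is wrong.** The instrument is described as adapted, so it may really have five points. In that case the Acceptability section misdescribes the scale, 4.0 is a demanding cut, and there is no leniency. Equally, the maximum of 5 in the table may be a slip, with 4.0 on 1–7 intended. This objection stands: a reader might infer that the scale is certainly 1–7 and that the cut should therefore be 5.5, but the text does not support that.

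**The conflict is narrower than three different rules.** The footnote and the Acceptability section give the same cut; only the table row departs from it. This is correct.

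**Indifferent users would rarely produce green.** A reader might infer that a group with no view either way would pass. Fifteen participants answering 4 throughout would indeed give 60% under the wording that allows equality. But if ratings scatter around 4.0, both subscales must pass, and the chance of green is only 0.02 to 0.04. Reading 4 as neutral also rests on the symmetry of the two end labels, since no middle label is given. What remains is that mildly positive ratings would often or nearly always pass.

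**The row does not decide progression alone.** It is one of nine rows. Table 2 adds qualitative and behavioural acceptability data in a note, and under Data analysis the Trial Management Committee judges the overall pattern. This softens the consequence but leaves the rule contradictory.

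**Timing is largely implied.** The past-tense follow-up items measure experienced acceptability, so a baseline reading is unlikely. Only the choice between 6 weeks and 3 months is open, and an analysis plan could settle that. It is a minor addition here.

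**Conclusion.** The contradiction is certain and needs no assumption: one progression threshold is stated with two scale maxima and two inequalities. Its consequence depends on the true scale.

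- **If the scale is 1–7,** the cut falls from 75% to 50% of the range and is lenient. For average ratings of about 4.5 to 5.0, the chance of green runs from 0.44 to above 0.99 at ≥4.0, and is about nil at the scale-equivalent 5.5. These probabilities rest on the two assumed spreads and on 25 completers. At higher averages the gap narrows: at 6.0 under spread A it is above 0.99 against 0.41.
- **If the scale is 1–5,** the cut is demanding and the Acceptability section needs correcting instead.

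The article does not show that the criterion would pass a group with no view, nor that 5.5 was the intended cut.

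**What to change.** Before any acceptability data are seen, confirm the response scale programmed in the questionnaire. Then state one scale, one cut and one inequality in the Table 2 row, its footnote and the Acceptability section.

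- If the scale is 1–5, correct the description in the Acceptability section and settle the inequality.
- If the scale is 1–7, correct the row. Then either raise the cut (5.5 keeps the stringency of 4.0 out of 5) or give a reason why 4.0 is the intended cut on that scale.
- Name the post-use, past-tense assessment (6 weeks or 3 months) that sets the colour.

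The cost is a wording change in three places, with no effect on recruitment, data collection or sample size. The downside is that the criterion may become harder to pass. At a cut of 5.5 with the 60% green band unchanged, a group averaging 5.5 under spread A would have 36% passing, which is red, and a group averaging 6.0 would have 56%, which is amber. The sponsor should therefore look at the cut and the percentage bands together.
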